### Quantitative hypotheses

In the Aim 2 efficacy test, we hypothesize that relative to adolescents in the comparison condition (detailed below), adolescents who participate in the adapted *Living in 2 Worlds* program will: (a) be less likely to initiate nicotine and cannabis vaping; (b) have lower vaping intentions, less permissive norms for vaping, be less vulnerable to offers, and perceive fewer benefits of vaping; (c) have better strategies for resisting vaping offers, risk assessment, decision making, and connecting with cultural values; and (d) experience similar reductions in desired alcohol, cigarettes, marijuana, and inhalants use/initiation as with the original version of *Living in 2 Worlds*. In addition, we hypothesize that youth who identify American Indian only will benefit more from the *Living in 2 Worlds* intervention than youth who identify as Multiracial/ Multiethnic. This hypothesis is based on two factors. First, youth identifying American Indian only are at greater risk for substance use, and research indicates that familial substance use has a stronger influence on cigarette use among American Indian only adolescents compare to their multiracial/multiethnic counterparts (48, 49). Second, the intervention is specifically designed to align with American Indian values, beliefs, and norms—elements that may have a stronger impact on youth who feel a closer connection to these cultural foundations. Prior research has noted that Multiracial/ Multiethnic Indigenous individuals often report weak ties to their Indigenous cultures and communities (50).

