**Figure 2 fig2:**
[figure not shown]
Study phases.

Phase 2 will use findings from the focus groups to adapt the *Living in 2 Worlds* intervention and pilot test with 11 urban Indigenous adolescents and the intervention facilitator in order to document the feasibility, acceptability, appropriateness, and utility of the adaptations.

Phase 3 will conduct a randomized controlled trial of the adapted *Living in 2 Worlds* intervention versus a comparison group with 360 urban Indgenous adolescents in ten public middle schools to test the hypotheses. Youth will be administered three surveys: pretest (T1 - September), an immediate post-test two months after implementation ends (T2 - January), at a time when the program effects on the prevention of short-term risks for vaping are expected to be strongest; and a follow-up posttest four months later (T3 – May).

Throughout all phases, an Indigenous Youth Advisory Board will be integrally involved to help guide the research. Successful strategies for engaging youth in active and meaningful ways in research studies will be evaluated, examining changes in youths’ confidence, leadership, and collaboration through pre-post surveys.

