### Comparison group

The comparison group will only complete surveys during the academic year on the same schedule as the *Living in 2 Worlds* intervention group. After RCT data collection is complete, the comparison group will have the opportunity to participate in *Living in 2 Worlds* at no cost during a summer camp implementation to ensure all adolescents have access to the curriculum.

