For all models, we will use the appropriate link function based on the level of measurement of the dependent variable. All models will control for demographic characteristics of participants where baseline equivalence between the treatment and comparison group are not achieved (e.g., sex, age, usual grades in school, two-parent household, receipt of free lunch at school), as well as control for school to adjust standard errors for the nested nature of the data (students nested in schools). Because of the small number of schools, multi-level models cannot be employed as they could lead to slightly inflated Type 1 error rates (75). We will adjust for missing data due to any attrition by employing full-information maximum likelihood (FIML) estimation. To determine if the null hypotheses should be rejected, effect sizes and their confidence intervals will assess the precision and substantive significance, and exact *p*-values will assess Type I error. We will also test if the adapted *Living in 2 Worlds* maintains effect sizes for other substance use seen in the original efficacy trial of *Living in 2 Worlds* (43). Based on a prior meta-analysis of universal substance use prevention programs for adolescents in grades 6 and 7, the overall average effect sizes were: *d* = 0.14 for smoking, *d* = 0.10 for alcohol use, and *d* = 0.14 for drug use (76). Based on this, we selected a non-inferiority margin of *d* = 0.14, which reflects approximately 50% of the effect size established in the original efficacy trial of *Living in 2 Worlds*.

We will test for moderation through interaction terms in general linear models (77) and multigroup analyses in latent change models (78). Multigroup analysis simultaneously tests separate models for each group. To test if parameter estimates of outcomes in the intervention conditions are equal across groups, we will use the chi-square difference test and compare model fit using model constraint methods for the main intervention effect path. A significant increase in chi-square between the two models (constrained-*M*_0_ vs. free-*M*_1_) indicates significant intervention effects between groups.

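### The d = 0.14 non-inferiority test against the original programme has no randomised comparator, and passing it would not show that the original effects are maintained

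*Protocol article*

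**What the plan says.** Hypothesis (d) in the protocol article's section on quantitative hypotheses expects that adolescents in the adapted programme will "experience similar reductions in desired alcohol, cigarettes, marijuana, and inhalants use/initiation as with the original version of" the programme. The statistical data analysis section turns this into a test of whether the adaptation "maintains effect sizes for other substance use seen in the original efficacy trial of" the programme. It then quotes meta-analytic average effects of 0.14 for smoking, 0.10 for alcohol and 0.14 for drug use, and continues: "Based on this, we selected a non-inferiority margin of" *d* = 0.14, which it describes as about half of the effect found in the original efficacy trial.

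The design has two arms. Under study design: "Phase 3 will conduct a randomized controlled trial of the adapted *Living in 2 Worlds* intervention versus a comparison group". The randomisation section assigns five schools to each arm. On the comparison arm: "The comparison group will only complete surveys during the academic year on the same schedule as" the intervention group. No arm receives the original version.

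The sample size section gives the only original effect in the document, *d* = 0.31, the average for cigarette and marijuana use. The section on the prevention intervention describes the original study as a small efficacy trial. No standard error or confidence interval is given for 0.31.

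**The concern.** A non-inferiority margin is a limit on the difference between a new treatment and a reference treatment. The reference here is the original programme, which is not delivered in this trial. The randomised contrast estimates adapted programme versus surveys only, and says nothing directly about adapted versus original. A statistical analysis plan could add the mechanics of a cross-trial comparison, but it could not supply the missing arm.

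At stake is the wording of the conclusion. A pass would be reported as the adapted curriculum having kept its effect on four substances. It would rest on a comparison between trials more than a decade apart (the original ended in 2012), against an imprecise benchmark, and with a margin that permits the loss of nearly half of the only original effect quoted. One margin also serves all four substances, although it equals the quoted average effect for smoking and for drugs and exceeds that for alcohol.

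**Working it through.** **Inputs from the article.** Margin 0.14; original effect 0.31; 360 adolescents in 10 schools, allocated 1:1; 20% attrition; pretest R² = 0.67; α = 0.05 (sidedness not stated).

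**Assumptions made here.** One-sided 2.5% for non-inferiority; R² = 0.67 also holds for other substance use; ICC 0.02 where clustering is shown; original standard error 0.05 to 0.20; normal approximation except where 8 df is stated.

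**1. The plan's own sample sizes.** Total completers = 4(1 − R²)(1.96 + 0.842)²/d².
- *d* = 0.31: 4 × 0.33 × 7.85/0.0961 = 108; 108/0.8 = 135, against the stated 132.
- *d* = 0.19: about 287, or 144 per arm = 288; 288/0.8 = 360, as stated.

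The same formula and inputs are therefore used below.

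**2. What a pass allows.** With 0.31 as benchmark, the lower confidence limit must exceed 0.31 − 0.14 = 0.17. The tolerated loss is 0.14/0.31 = 45%. For alcohol and inhalants no original effect is quoted, so the tolerated loss cannot be computed. The margin is larger than the quoted average alcohol effect (0.14 against 0.10).

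**3. Precision.** Completers = 360 × 0.8 = 288. SE(*d*) = √(4 × 0.33/288) = 0.0677. With 28.8 completers per school and ICC 0.02, the design effect is 1 + 27.8 × 0.02 = 1.556, so SE = 0.0677 × √1.556 = 0.0844.

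**4. Chance that a fully preserved effect passes (true *d* = 0.31, benchmark treated as known).**
- Unclustered: the observed *d* must reach 0.17 + 1.96 × 0.0677 = 0.30. Probability = Φ(0.14/0.0677 − 1.96) = 54%. At one-sided 5% it is 66%.
- ICC 0.02, noncentral *t* with 8 df (critical value 2.306): 31%.

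**5. Error rate if the estimate 0.31 is treated as known.** Take a true adapted effect exactly 0.14 below the true original effect. The chance of a false pass is 1 − Φ(1.96 × SE/√(SE² + SE₀²)), with SE = 0.0677 and SE₀ the original trial's standard error.

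| Assumed SE₀ | Actual one-sided error (nominal 2.5%) |
|---|---|
| 0.05 | 6% |
| 0.10 | 14% |
| 0.15 | 21% |
| 0.20 | 26% |

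Carrying SE₀ into the interval restores the error rate but lowers the chance that a preserved effect passes, Φ(0.14/√(SE² + SE₀²) − 1.96), to 38%, 21%, 13% and 10% for the same four values (unclustered).

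**The case against.** The text names the original trial as the reference, so the test is a cross-trial comparison and not a claim of non-inferiority to the survey-only arm. This stands. A reader might infer that a programme with no effect could be declared non-inferior simply because the only other arm is untreated. The document does not describe that test. Against a bound of 0.17, a zero-effect programme would pass with probability Φ(−0.17/0.0677 − 1.96), about 0.0004%, and about 0.008% at ICC 0.02 with 8 df.

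An indirect comparison is also legitimate in principle, and the article offers some support for it: other substance use is measured with items from the earlier study, and the community partner and the urban Indigenous middle-school population are the same. This stands too, and it is why the fix leaves room for an exploratory comparison. It does not make the comparison randomised, and the earlier trial's comparator is not described.

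A further possible reading is that 0.14 is itself the effect to be retained, so that the effect versus survey-only must exceed 0.14. A true effect of 0.31 would then pass 71% of the time unclustered (43% at ICC 0.02 with 8 df). That reading would permit an even larger loss, (0.31 − 0.14)/0.31 = 55%.

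Two more points are fair. The article does not say which original effect the margin halves: 0.14 is exactly half of 0.28, and 45% is within what approximately 50% can mean. And power for this test, like the detailed mechanics, may sit in documents not shown. Neither is counted as an error here.

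**Conclusion.** The concern holds as a defect in what the article states. The planned conclusion about maintaining the original effects cannot come from the randomised contrast. With 0.31 as benchmark, a pass is compatible with losing about 45% of the effect. That figure rests on 0.31 being the intended benchmark, the only one the document offers. The error inflation to 6–26% rests on an assumed original standard error and applies only if the estimate is treated as known, which the article neither states nor rules out.

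A reader might also infer that a fully preserved effect would usually fail. The article's own inputs do not show this: unclustered, it passes slightly more often than not (54%). It falls below half only with an assumed ICC (31% at 0.02 with 8 df) or an assumed standard error for the original estimate.

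Severity is should-fix. Hypothesis (d) is secondary to the vaping aims, whose analyses are unaffected.

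**What to change.** Remove the confirmatory non-inferiority conclusion and its margin. Reword hypothesis (d) as a reduction in each substance relative to the comparison group. For alcohol, cigarettes, marijuana and inhalants separately, estimate and test adapted programme versus survey-only, and report *d* with a 95% CI.

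Show the original trial's estimate and CI alongside, descriptively. If a comparison with the original is kept, label it an exploratory indirect comparison, give a benchmark and margin for each substance, carry the original estimate's standard error into the interval, and state why the earlier effect is expected to carry over.

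The change is to the wording of one hypothesis and one analysis paragraph, and needs no new arm, data or participants. The cost is that the sponsor gives up a confirmatory claim of non-inferiority to the original programme.

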#### Additional substance use

Youths’ self-reports of recent (last 30 days) frequency and amount of alcohol, cigarettes, marijuana (excluding cannabis vaping), and inhalants will be measured with items from the prior *Living in 2 Worlds* study (43).

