#### Sample size calculations

Sample size calculations for the main effects of the intervention were estimated from the average effect of cigarette and marijuana use in the original *Living in 2 Worlds* efficacy trial (*d* = 0.31) and through a systematic review of school-based e-cigarette preventive interventions (*d* = 0.47). With a sample size of 132 adolescents, an effect size *of d* = 0.31 can be detected with 0.80 power for a significant intervention difference assuming a Type I error rate of *d* = 0.31, *α* = 0.05, given a pretest R^2^ = 0.67 and a 20% attrition rate. Effect sizes for the moderation analysis were estimated comparing alcohol use of urban Indigenous students who self-identified as American Indian only to students who self-identified as multiracial/ multiethnic (OR = 1.41; *d* = 0.19) (48). Assumingα = 0.05, a pretest R^2^ = 0.67, and a 20% attrition rate, we will have 80% power to detect *d* = 0.19, for statistically significant moderated intervention effects with 360 urban Indigenous adolescents ages 11–14.

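### The single non-inferiority margin of d = 0.14 is not supported for alcohol or inhalants: it exceeds the plan's own alcohol average, and the only original-trial effect shown covers cigarettes and marijuana.

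*Protocol article*

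**What the plan says.** Under Quantitative hypotheses, item (d) expects participants to "experience similar reductions in desired alcohol, cigarettes, marijuana, and inhalants use/initiation as with the original version". Four substances are named. The measures section (Additional substance use) confirms that recent "frequency and amount of alcohol, cigarettes, marijuana (excluding cannabis vaping), and inhalants will be measured".

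Under Statistical data analysis plans, the test is whether the adapted programme "maintains effect sizes for other substance use seen in the original efficacy trial". The benchmark is thus the original trial's effect. The same paragraph cites meta-analytic averages for universal programmes (smoking 0.14, alcohol 0.10, drug use 0.14) and, on that basis, fixes one value, to which it adds a second rationale: "we selected a non-inferiority margin of *d* = 0.14, which reflects approximately 50% of the effect size established in the original efficacy trial". No substance is named there, and no margin is given for an individual substance.

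The article shows one effect from the original trial, under Sample size calculations. The main-effect calculation was "estimated from the average effect of cigarette and marijuana use in the original *Living in 2 Worlds* efficacy trial (*d* = 0.31"). Alcohol and inhalants are not part of that average.

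**The concern.** A non-inferiority margin should be smaller than the effect it protects, and its justification should refer to the endpoint it is used for. Here one number serves four endpoints and rests on two anchors. The first, the meta-analysis, gives alcohol a smaller average than the margin. The second, about half of the original effect, can be checked only against a figure that leaves out alcohol and inhalants.

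At stake is what a conclusion of maintained effect would mean for those two substances. Depending on the original effect, it could be compatible with losing most or all of the benefit, although the stated rationale is to keep about half.

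**Working it through.** **The plan's own figure.** Inputs from Sample size calculations: pretest R² = 0.67, α = 0.05 (taken as two-sided), power 0.80, attrition 20%. The allocation is 1:1, from Randomization of schools.

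- Per arm, n = 2(1 − R²)(1.96 + 0.8416)² / d².
- d = 0.19: 2 × 0.33 × 7.849 / 0.0361 = 143.5, so 144 per arm and 288 in total; 288 / 0.8 = 360, as stated.
- d = 0.31: 54 per arm and 108 in total; 108 / 0.8 = 135, against 132 stated (within 3%).

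The inputs are therefore read as the plan intends, with 144 per arm left after attrition.

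**The margin against its two anchors.**

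- Meta-analysis: 0.14 / 0.10 = 140% of the alcohol average; 0.14 / 0.14 = 100% of the smoking and drug averages.
- Original trial: 0.14 / 0.31 = 45% of the cigarette and marijuana average. For 0.14 to be exactly half, the original effect must be 0.14 / 0.5 = 0.28.

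**What the margin accepts, by original effect.** The smallest accepted effect is the reference minus 0.14, and the share given up is 0.14 / reference. For the pass rate of a programme with no effect, SE(d) = √(2 × 0.33 / 144) = 0.0677, and

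P(pass | true effect 0) = Φ(−(reference − 0.14)/SE − 1.96).

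This uses one-sided 2.5%, treats the reference as fixed and ignores clustering.

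| Original effect (assumed) | Smallest accepted effect | Share given up | P(pass, no effect) |
|---|---|---|---|
| 0.10 | −0.04 | 140% | 8.5% |
| 0.14 | 0.00 | 100% | 2.5% |
| 0.20 | +0.06 | 70% | 0.2% |
| 0.28 | +0.14 | 50% | 0.003% |
| 0.31 | +0.17 | 45% | below 0.003% |

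For the first row: 0.04 / 0.0677 = 0.591, and Φ(0.591 − 1.96) = 0.0855. With an assumed ICC of 0.02 and 36 × 0.8 = 28.8 pupils analysed per school, the design effect is 1 + 27.8 × 0.02 = 1.556, the SE is 0.0844, and the pass rate is 6.9%.

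**Cigarettes and marijuana.** Since 0.31 is an average of two effects, one of them falls below 0.28 whenever the other exceeds 2 × 0.31 − 0.28 = 0.34. The average alone does not show that 0.14 is at most half of each.

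**What this trial could test.** With one-sided 2.5% and 80% power, n per arm = 2 × 0.33 × 7.849 / margin². A margin of 0.14 needs 265 per arm and a margin of 0.05 needs 2,073, against 144 available.

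**The case against.** The strongest reply is that the benchmark is the original trial, not the meta-analysis. The 0.10 is an average over universal programmes and need not be the alcohol effect of this one. Read literally, about 50% implies an original effect near 0.28, and at that value a null programme almost never passes. The article also does not say which substances lie behind the effect it halves. This reply stands as far as it goes: the article does not show that the original alcohol effect is below 0.14. But it does not show that the effect is near 0.28 either, and the one alcohol figure it cites is about a third of that.

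A second reply is that judging alcohol by the meta-analysis and cigarettes by the original trial is selective. That is fair. By the meta-analytic yardstick, the margin gives up the whole smoking and drug effects too, so cigarettes and marijuana also need checking, each on its own original effect.

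A third reply is that effects by substance may stand in a full protocol or SAP that is not shown, and that this is the last of the lettered hypotheses. Both points limit the weight of the finding. They do not remove it, because the article itself fixes the margin and gives the rationale, and the two do not fit together for alcohol.

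A reader might also take the 8.5% as an inflated Type I error. It is not. With a threshold of −0.04, zero effect belongs to the non-inferiority alternative, and the nominal 2.5% applies at −0.04. The figure is a pass rate under an assumed reference, and a null programme would still fail about 91% of the time.

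**Conclusion.** The point holds in conditional form. One margin of 0.14 is fixed for four substances. It exceeds the plan's alcohol average, equals the whole of its smoking and drug averages, and is linked to an original-trial effect only for cigarettes and marijuana. It is therefore not supported for alcohol or inhalants.

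How much this matters turns on an original alcohol effect that the article does not give:

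- below 0.14, no effect on alcohol lies inside the margin;
- from 0.14 to just under 0.28, no effect is not inside the margin, but more than half of the benefit is given up, contrary to the stated rationale;
- at about 0.28 or more, the rationale holds.

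A reader might infer outright that the plan would accept a programme with no effect on alcohol. The documents do not support that, because it rests on using 0.10 in place of the missing original effect. For the same reason, 0.05 is not offered as the right alcohol margin: it is half of a meta-analytic value, not of the original effect. The 8.5% is illustrative. It assumes a reference of 0.10, 288 analysed, R² = 0.67, no clustering and no uncertainty in the historical effect.

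**What to change.** State the original trial's effect for each of the four substances. Set each margin at no more than half of that substance's own original effect. Keep 0.14 only where that effect is about 0.28 or more, checking cigarettes and marijuana separately and not through their average. Where the original effect is too small to give a margin that this trial can test, report the effect and its confidence interval and make no non-inferiority claim.

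This is a change of wording before Phase 3 and needs no new data. The cost is in what can be concluded. Tighter margins make a finding of maintained effect harder or impossible to reach for alcohol and possibly inhalants, and the sample is already below what a margin of 0.14 needs for 80% power.

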#### Sample size calculations

Sample size calculations for the main effects of the intervention were estimated from the average effect of cigarette and marijuana use in the original *Living in 2 Worlds* efficacy trial (*d* = 0.31) and through a systematic review of school-based e-cigarette preventive interventions (*d* = 0.47). With a sample size of 132 adolescents, an effect size *of d* = 0.31 can be detected with 0.80 power for a significant intervention difference assuming a Type I error rate of *d* = 0.31, *α* = 0.05, given a pretest R^2^ = 0.67 and a 20% attrition rate. Effect sizes for the moderation analysis were estimated comparing alcohol use of urban Indigenous students who self-identified as American Indian only to students who self-identified as multiracial/ multiethnic (OR = 1.41; *d* = 0.19) (48). Assumingα = 0.05, a pretest R^2^ = 0.67, and a 20% attrition rate, we will have 80% power to detect *d* = 0.19, for statistically significant moderated intervention effects with 360 urban Indigenous adolescents ages 11–14.

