### Phase 3: Randomized controlled trial (RCT) of the vaping adaptation of living in 2 worlds

#### Randomization of schools

Ten middle schools in the Phoenix metropolitan area that have a Native American Education Program will be invited to participate in the study over the course of two cohorts (one cohort per school year). The Native American Education Program is administered by the Office of Indian Education at the Arizona Department of Education with the goal of supporting academic and culture needs of Native American students in Arizona. Schools will be randomly assigned into either: (1) *Living in 2 Worlds* Intervention (5 schools; 180 adolescents; 36 per school) or (2) Comparison group (5 schools; 180 adolescents; 36 per school).

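### The sample size calculation ignores randomisation by school: the 80% power stated for 132 adolescents does not hold for ten schools, and power for the 360 enrolled depends on an unstated ICC

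*Protocol article*

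**What the plan says.** Under Randomization of schools, the article makes the school the unit of allocation: "Schools will be randomly assigned into either" the intervention or the comparison group, with "5 schools; 180 adolescents; 36 per school" in each arm. That is ten schools and 360 pupils.

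Under Sample size calculations it states: "With a sample size of 132 adolescents", an effect size of d = "0.31 can be detected with 0.80 power for a significant intervention difference". The inputs listed are alpha = 0.05 and the terms in "given a pretest R^2^ = 0.67 and a 20% attrition rate". With the same alpha, R² and attrition it adds that "we will have 80% power to detect" d = 0.19 for moderated effects with 360 adolescents. No ICC, design effect, cluster size or school-level degrees of freedom enters either statement.

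Under Statistical data analysis plans it recognises that students are nested in schools, intends to adjust standard errors for this, and rules out multilevel models because there are few schools. The same section says, in the context of the analysis by sex, that the study is powered for differences above d = 0.31.

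**The concern.** When schools are randomised, the precision of the treatment contrast depends on how much schools differ and how many there are, as well as on the number of pupils. A formula for independent pupils sets between-school variance to zero and uses a normal or large-sample critical value. With five schools per arm, both choices overstate power.

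This paragraph is the article's quantitative justification for the trial's size. Readers and the monitoring board would take it that 132 pupils suffice for d = 0.31, so that 360 leaves a wide margin. If that margin is not real, a null main effect would be read as stronger evidence of no effect than the design can give.

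**Working it through.** **Inputs from the article.** Ten schools, 36 enrolled per school; d = 0.31; alpha 0.05 (sidedness not stated, two-sided assumed); power 0.80; pretest R² = 0.67, so residual variance 1 − 0.67 = 0.33; attrition 20%.

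**Assumptions added here.** ICC of 0 to 0.05. Pretest R² at school level of either 0.67 or 0. A school-level reference distribution with 10 − 2 = 8 df.

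**Step 1: reproduce the stated sizes without clustering.** N = 4(1.96 + 0.84)² × 0.33 / d², where (1.96 + 0.84)² = 7.849 before rounding.

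- d = 0.31: 4 × 7.849 × 0.33 / 0.0961 = 107.8, so 108 evaluable; 108 / 0.8 = 135. The t-based version needs 55 per arm, and 110 × 1.2 = 132, the printed figure.
- d = 0.19: 4 × 7.849 × 0.33 / 0.0361 = 287.0, or 288 with 144 per arm; 288 / 0.8 = 360, the printed figure.

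The exact attrition convention behind 132 is inferred, but neither figure leaves room for a design effect above 1.

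**Step 2: the same effect with ten schools.** With m pupils retained per school,

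Var = (4/10) × [ICC × (1 − R²between) + (1 − ICC) × 0.33 / m],

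and power is the upper tail of a non-central t with 8 df and non-centrality 0.31/√Var, beyond 2.306. The 80%-power detectable d is 3.20 × √Var.

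*132 recruited:* 132 × 0.8 = 105.6 retained, m = 10.56. At ICC 0, Var = 0.4 × 0.33 / 10.56 = 0.0125, SE = 0.112, non-centrality 2.77, power 68%.

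| ICC | Power, d = 0.31 (R²between 0.67) |
|---|---|
| 0 | 68% |
| 0.02 | 61% |
| 0.05 | 52% |

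*360 enrolled:* 360 × 0.8 = 288 retained, m = 28.8. Example at ICC 0.02 and R²between 0.67: Var = 0.4 × [0.0066 + 0.0112] = 0.00713, SE = 0.0844, non-centrality 3.67, power 89%.

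| ICC | Power (R²between 0.67) | Detectable d | Power (R²between 0) | Detectable d |
|---|---|---|---|---|
| 0 | 98% | 0.22 | 98% | 0.22 |
| 0.01 | 94% | 0.25 | 84% | 0.30 |
| 0.02 | 89% | 0.27 | 68% | 0.36 |
| 0.05 | 74% | 0.34 | 42% | 0.50 |

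Power at d = 0.31 with 360 enrolled falls to 80% at an ICC of about 0.038 (R²between 0.67) or about 0.012 (R²between 0).

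**Step 3: how much rests on the 8 df.** Replacing the t reference by a normal one (critical value 1.96), with R²between 0.67, gives for 132 recruited 79%, 72% and 63% at ICC 0, 0.02 and 0.05. For 360 enrolled it gives 98%, 96% and 84% at ICC 0.01, 0.02 and 0.05.

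**The case against.** The strongest reply is that 132 is not the trial. The article enrols 360, a number driven by the moderation analysis, and nobody plans to spread 132 pupils over ten schools. For the enrolled sample, power at d = 0.31 is 89% or more up to an ICC of 0.02 if the pretest works equally well at school level. This stands. A reader might infer from the missing clustering that the trial is underpowered for its main effect. The article does not support that inference, because the answer turns on an ICC and a between-school R² that it does not give.

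A reader might also infer that clustering refutes the d = 0.19 claim, or that the trial's detectable main effect worsens from 0.19. Neither follows. The article gives 0.19 only for moderation by racial/ethnic identity. That is a pupil-level variable that can vary within schools, so the school-level 8-df calculation does not directly apply to it. Whether a two-group formula suits an interaction is a separate question. The stated main-effect target is 0.31.

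The 8 df are an analytic choice made here; the article says only that models will control for school. Without them the 132 figure is close to right at an ICC of exactly zero (79%), though it falls short at the positive ICCs examined.

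Finally, a condensed article may leave an ICC justification to a fuller document. That would excuse missing detail. It does not excuse printed figures that come out of their printed inputs only when clustering is absent.

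**Conclusion.** The point holds for the main-effect power statement. The article sizes a school-randomised trial as if pupils were randomised, although it recognises the nesting in its analysis section. On a school-level test, the 80% claimed for 132 adolescents is at most 68%, and 52% at an ICC of 0.05.

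For the 360 to be enrolled, the claim of power above d = 0.31 is conditional, not wrong outright. It holds below an ICC of about 0.038 if the pretest explains 67% of between-school variance, and below about 0.012 if it explains none. These figures rest on assumed ICCs, two-sided alpha 0.05, equal school sizes, 20% attrition spread evenly over schools, and 8 df.

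**What to change.** Delete the 132-adolescent statement. Restate main-effect power at d = 0.31, and the d detectable with 80% power, for ten schools with 36 enrolled and about 29 retained per school. Give an explicit ICC range with its source, a stated assumption about how much between-school variance the pretest explains, and school-level degrees of freedom. Reword the sentence in Statistical data analysis plans that calls the study powered above d = 0.31 so that it carries the same conditions. Where the paragraph prints the Type I error rate as d = 0.31 before giving alpha, correct that slip and state the sidedness. Treat the d = 0.19 moderation statement separately.

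The cost is one rewritten paragraph and one aligned sentence, best done before Phase 3 is registered. Design and recruitment are unchanged. What is lost is the apparent margin between 132 and 360.
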